# A prospective, randomized, single-blind, multicentre, phase III study on organ preservation with Custodiol-N solution compared with Custodiol® solution in organ transplantation (kidney, liver and pancreas)

**DOI:** 10.1186/s13063-019-3823-4

**Published:** 2020-01-10

**Keywords:** Preservation solution, Liver transplantation, Kidney transplantation, Pancreatic transplantation

## Abstract

**Background:**

Organ preservation before transplantation is still a challenge. Both the University of Wisconsin and Bretschneider’s histidine-tryptophan-ketoglutarate (HTK; Custodiol®) solution are standard for liver, kidney and pancreas preservation. Organ preservation with both solutions is comparable; recently, however, Custodiol® solution has been modified to Custodiol-N according to the needs of today. Thus, our study was defined to study its effect in clinical transplantation.

**Methods:**

Patients undergoing kidney transplantation (*n* = 412) (including approximately 30 combined kidney–pancreas) or liver transplantation (*n* = 202) receive grafts that have been cold stored in either Custodiol® or Custodiol-N to demonstrate noninferiority of Custodiol-N regarding both graft function and graft injury after transplantation.

**Discussion:**

Preclinical data have clearly shown that Custodiol-N is superior to Custodiol® in cold static organ preservation via mechanisms including inhibition of hypoxic cell injury, cold-induced cell injury and avoidance of adverse effects during warm exposure to the solution. Further clinical safety data on Custodiol-N for cardioplegia are available. Thus, this study was designed to compare Custodiol® with Custodiol-N for the first time in a prospective, randomized, single-blinded, multicentre, phase III clinical transplantation trial.

**Trial registration:**

Eudra-CT, 2017–002198-20. Registered on 28 November 2018.

## Introduction

Bretschneider’s histidine-tryptophan-ketoglutarate (HTK; Custodiol®) solution was developed at the end of the 1970s and was first used in the setting of cardiac surgery as a cardioplegic solution in 1982. At the beginning of the 1980s, the solution began to be used for other purposes; first for kidney preservation, and later for liver and pancreas preservation as well. Since 2000, additional knowledge has been gained on the mechanisms of cell and tissue injury during cold ischemia. Based on these experimental findings, traditional Custodiol® solution has been modified to Custodiol-N (for the components of each, see Table 1).

**Table 1 Tab1:** Components of Custodiol® and Custodiol-N

	Custodiol® (mmol/L)	Custodiol-N (mmol/L)
Sodium	16	16
Potassium	10	10
Magnesium	4	8
Calcium	0.015	0.020
Chloride	50	30
L-Histidine	198	124
N-α-acetyl-L-Histidine	–	57
Tryptophan	2	2
α-Ketoglutarate	2	2
Aspartate	1	5
Arginine	–	3
Alanine	–	5
Glycine	–	10
Mannitol	30	–
Sucrose	–	33
Deferoxamine	–	0.025
LK-614	–	0.0075

It has been shown in several cell types that the amino acids glycine and alanine provide protection against hypoxic or ischemic cell injury [1–7] which is attributed to a pathological membrane pore forming under hypoxic conditions and leading to alterations of the cellular ion homeostasis [3, 5, 8]. Furthermore, it has become clear that hypothermia, used to protect tissues against ischemic injury, also triggers injury on its own account [9–13]. This cold-induced cell injury affects numerous cell types but, in particular, affects endothelial cells, jeopardizing vascular function after reperfusion, and is mediated by intracellular “redox-active” iron [11, 14–16]. Based on these experimental findings, the traditional Custodiol® solution was fortified with the amino acids glycine and alanine to inhibit the formation of the hypoxia-induced plasma membrane pore. Furthermore, it was supplemented by the strong, but poorly membrane-permeable, iron chelator deferoxamine and the new, membrane-permeable iron chelator LK-614 to inhibit cold-induced cell injury.

Furthermore, recent studies have shown that the buffer histidine, essential for the efficiency of Custodiol® (see above), can have adverse effects on some cell types rich in “redox-active” iron, particularly if used at very high concentrations [17]. The histidine derivative N-acetyl-histidine does not display these adverse effects but has a similar buffering power to histidine. Therefore, part of the histidine in Custodiol® (as much as possible without altering the successful ion composition of the solution) was replaced by the superior derivative N-acetyl-histidine.

Microcirculatory disturbances have been reported following reperfusion of diverse organs. In various experimental models, the troublesome application of the vasodilator nitric oxide or simply the supplementation of L-arginine (the substrate of the endogenous nitric oxide-producing enzymes) has been proven to decrease these microcirculatory disturbances [18–21]. Therefore, in Custodiol-N, L-arginine is supplemented. As mannitol is not impermeable to all cell types (i.e. hepatocytes [22]), it has been replaced with saccharose. Although efficient buffering is important to prevent severe acidosis, moderate acidosis has been shown to provide protection against ischemic injury [23, 24]; therefore Custodiol-N has a slightly lower pH than Custodiol®. Finally, aspartate has been added to replenish intermediates of the tricarboxylic acid cycle in combination with the ketoglutarate that is already present in Custodiol® for an efficient energy production after reperfusion. Besides these alterations, the successful composition of Custodiol® has been maintained.

This amino acid-fortified and iron chelator-supplemented Custodiol-N proved to be superior to Custodiol® in in vitro studies using diverse cell types; in particular, Custodiol-N showed far superior inhibition of hypoxic cell injury, superior to far superior inhibition of cold-induced cell injury, and avoidance of adverse effects; this was also seen during warm exposure to the solution [14, 25].

In a study on the isolated perfused rat heart (Langendorff model), a protective effect towards the injury to the coronary vasculature inflicted by cold ischemia was shown by the iron chelators deferoxamine and LK-614, that is the iron chelators present in Custodiol-N [26].

A further study demonstrated that Custodiol-N protects liver grafts with microvesicular steatosis caused by acute toxic injury from cold ischemic injury better than Custodiol®, most likely via inhibition of hypoxic injury and oxidative stress and amelioration of the inflammatory reaction occurring upon reperfusion [27].

## Objectives

The objective of this clinical trial is to demonstrate noninferiority of graft preservation with Custodiol-N compared to Custodiol® with respect to both graft function and injury after transplantation of kidney, liver or combined kidney–pancreas.

### Primary end points

#### Kidney

The primary end point after kidney transplantation is delayed graft function, defined as dialysis requirement during the first week after transplantation.

#### Liver

After liver transplantation, the primary end point is the area under the curve (AUC) of alanine aminotransferase (ALT) during the first 7 days after surgery (minimum one measurement per day).

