#### Patient (recipient) criteria

Patients (≥18 years) eligible for whole organ transplantation are included in the study.

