#### Liver recipients

Machine-perfused organs are excluded from the study as well as recipients undergoing re-transplantation.

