#### Screening of the recipient

The screening visit includes a check of the inclusion and exclusion criteria (to test female patients ≤55 years for pregnancy), assessment of demographic data (age and gender) of the recipient, and informed consent. Within 24 h before transplantation, the recipients’ clinical status (calculated model for end-stage liver disease score) and the recipients’ routine laboratory results (serum bilirubin, AST, ALT, LDH, total albumin) are assessed. Additionally, the occurrence of adverse advents and concomitant medication will be recorded. Events compromising the blinding of the patient will be recorded as protocol deviations.

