#### Liver

The success of liver transplantation is determined by the AUC of ALT measurements over the first 7 days after implantation. In a sample of 25 consecutively treated patients, the ALT level in the period between surgery and 5 days had an AUC of about 3800 mg*d/dl with a standard deviation of about 2000 mg*d/dL. Assuming a coefficient of variation of 0.5, in order to reject the hypothesis that the peak level rises by 25% or more at the alpha level of 0.025 with a power of 90%, 202 patients are needed. For sample size calculation, a two-sample *t* test of the mean ratio with lognormal data was used.

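### The liver primary end point is an uncorrected 7-day ALT AUC open to recipients with very high pre-transplant ALT, and the recorded pre-transplant value is given no role

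*Protocol article*

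**What the plan says.** All references are to the protocol article.

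- **End point** (Primary end points, Liver): "the primary end point is the area under the curve (AUC) of alanine aminotransferase (ALT) during the first 7 days after surgery". There is no baseline subtraction, ratio to baseline or other correction.
- **Eligibility** (Inclusion criteria, Patient (recipient) criteria): "Patients (≥18 years) eligible for whole organ transplantation are included in the study".
- **Exclusions** (Liver recipients): "Machine-perfused organs are excluded from the study as well as recipients undergoing re-transplantation". The general and recipient exclusions add previous transplantation, pregnancy or lactation, another interventional study, and combined allocations other than kidney with pancreas. None limits pre-transplant ALT or the underlying liver diagnosis.
- **Data collected** (Liver, Screening of the recipient): within 24 h before transplantation, "the recipients’ routine laboratory results (serum bilirubin, AST, ALT, LDH, total albumin) are assessed". Donor ALT is also recorded (Liver, Screening of donor and graft status).
- **Method** (Sample size determination, Liver): a two-sample t "test of the mean ratio with lognormal data was used", named for the sample size calculation. Its inputs are a pilot series of 25 consecutive patients whose ALT "had an AUC of about 3800 mg*d/dl with a standard deviation of about 2000 mg*d/dL", and the planning value "Assuming a coefficient of variation of 0.5". The margin is a 25% rise, alpha 0.025, power 90%, 202 patients.
- **Decision rule** (Analysis sets): the kidney and liver tests must both succeed.

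**The concern.** The Objectives section is about graft function and graft injury. ALT circulating at the end of surgery can include enzyme from the explanted liver, which then clears over the following days inside the AUC window. It says nothing about the preservation solution. For a recipient with near-normal ALT the contribution is small. For one who starts in the thousands it can exceed the whole planned mean AUC.

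Two things are at stake. First, a few such recipients widen the spread of log AUC, and by chance they may fall unevenly between arms. That moves the estimated ratio either way against a 25% margin. Second, an amount unrelated to the solution is added to both arms and pulls the ratio toward 1. In a noninferiority trial that pull helps the new product.

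**Working it through.** **1. The plan's own figure.** With CV 0.5, the SD of log AUC is √ln(1 + 0.5²) = 0.472. With margin ln 1.25 = 0.223, one-sided alpha 0.025, power 90% and true ratio 1, n per arm = 2 × 0.472² × (1.960 + 1.282)² / 0.223² ≈ 95. That is 190 in total, or 192 with the t distribution. The stated 202 gives 91.6% power, so it is slightly generous for its inputs. With the pilot CV of 2000/3800 = 0.526 the need is 210, and 202 gives 89.1%. The point does not depend on this difference.

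**2. Carry-over for one recipient.** The documents give no ALT clearance, so I assume first-order decay with a half-life of 1 to 3 days and no surgical wash-out. I read 3800 as ALT units × days, although it comes from a 5-day window.

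Carry-over = ALT₀ × (1 − e^(−7k))/k, with k = ln 2 / half-life. At 2 days the multiplier is 2.63.

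| Pre-transplant ALT | Half-life 1 d | 2 d | 3 d | Share of 3800 |
|---|---|---|---|---|
| 50 | 72 | 132 | 173 | 2–5% |
| 200 | 286 | 526 | 694 | 8–18% |
| 1000 | 1431 | 2630 | 3469 | 38–91% |
| 3000 | 4294 | 7891 | 10408 | 113–274% |

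**3. Dilution for one recipient.** If the graft part is truly 25% higher (4750 against 3800) and the native part is equal, then at a 2-day half-life:
- ALT 50: (4750 + 132)/(3800 + 132) = 1.24
- ALT 1000: (4750 + 2630)/(3800 + 2630) = 1.15
- ALT 3000: (4750 + 7891)/(3800 + 7891) = 1.08

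**4. The whole trial, by simulation.** Setup: 101 per arm, graft AUC lognormal with mean 3800 and CV 0.5, half-life 2 days, no wash-out. A given share of recipients starts at ALT 500–5000 and the rest near 50. All of this case mix is assumed. The error column is the one-sided chance of declaring noninferiority when the graft-derived ratio is truly 1.25.

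| Share with high ALT | Power, unadjusted | Power, adjusted for log ALT | Error, unadjusted / adjusted |
|---|---|---|---|
| 0% | about 94% | about 94% | 0.035 / 0.035 |
| 2% | about 1 point lower | about 93% | 0.037 / 0.038 |
| 5% | about 90% | about 94% | 0.040 / 0.041 |
| 10% | about 87% | about 94% | 0.047 / 0.052 |

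With 50% wash-out and a 10% share, power is about 89–91% unadjusted and 93% adjusted.

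Two readings of this table matter. The 94% exceeds the 91.6% of step 1 only because residual ALT in everyone compresses log AUC, which is itself dilution and not a gain. For the same reason the error is already 0.035 with no high-ALT recipients. The covariate restores power but leaves the error where it was or slightly higher, because carry-over adds on the raw scale while the covariate acts on the log scale.

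**5. Wider range.** With 2–10% of recipients centred on ALT 1000 or 3000 and half-lives of 1 to 3 days, power at 202 runs from 74% to 94%. A graft ratio of 1.25 appears as 1.22–1.24, and the error is about 0.03–0.05.

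**The case against.** The strongest reply is that this belongs to the analysis plan. The article condenses a full protocol, the SAP is not shown, and the t test is named only for sample size, where an unadjusted calculation is routine even if the analysis adjusts. A reader might infer that the trial will ignore pre-transplant ALT. The documents do not support that: they are silent on the analysis model. What stands is narrower. The end point definition belongs to the protocol, it carries no baseline correction, and eligibility does not limit the value.

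A reader might also infer bias between the arms. Randomised 1:1 allocation rules out a systematic difference in a value measured before the study solution can act. Chance imbalance is already covered by the 0.025 level for the AUC as defined. The raised error in the table concerns the graft-derived ratio, not the stated AUC hypothesis.

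Third, the size is assumed throughout, and some of the loss may be counted twice. The pilot patients were consecutive and their AUC ran from surgery, so the SD of 2000 may already include native-liver ALT. In that case adjustment is a gain in precision, not the repair of a shortfall. This stands.

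Finally, it is tempting to say that adjustment removes the problem. It deals with the noise and chance imbalance, but not with the dilution.

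**Conclusion.** The point holds in limited form. As defined, the liver primary end point can contain native-liver ALT, the criteria admit recipients in whom that part is large, and the article gives the recorded pre-transplant value no role.

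Under a 2-day half-life and no wash-out, the cost is about 1 point of power at a 2% share of high-ALT recipients and about 7 points at 10% (94% to 87%). It is less with wash-out or if the pilot SD already reflects such cases. Dilution is modest in the aggregate (1.25 seen as about 1.22–1.24) but acts toward declaring noninferiority.

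The documents give neither the case mix nor the clearance, so they do not show that the liver comparison is underpowered or biased. They show an avoidable weakness in an end point on which the overall result depends, since liver and kidney must both succeed and no patients are added for attrition.

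**What to change.** 1. Prespecify the liver primary analysis as an ANCOVA of log(AUC) on arm, with log recipient ALT within 24 h before transplantation as covariate. Keep the 25% ratio margin.
2. Log donor ALT may be added for precision only, since it has no bearing on native-liver carry-over.
3. Keep the unadjusted t test on log AUC as a sensitivity analysis.
4. Because the covariate does not remove the dilution, prespecify a further sensitivity analysis without recipients whose pre-transplant ALT exceeds a threshold fixed before the data are seen. In the model above this brings the error back to the level of the 0% row, about 0.035. The rest comes from ordinary residual ALT in all recipients.

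If the unseen SAP already contains the covariate, only the fourth item may be new. The cost is a few sentences in the protocol or SAP. The values are already collected, so no patients, visits or measurements are added. The text must be fixed before the data are seen, because a covariate or exclusion chosen afterwards would not be credible in a noninferiority comparison.

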### Secondary objectives

#### Kidney

The secondary objectives after kidney transplantation are the incidence of primary poor function defined as creatinine >250 μmol/l after 90 days, serum creatinine, creatinine modification of diet in renal disease (MDRD) clearance, urea and haemoglobin after 90 days, and the requirement for dialysis until 90 days after transplantation, as well as biopsy-proven rejection.

#### Combined kidney–pancreas

The secondary end points after pancreatic transplantation include insulin requirements on postoperative days 3, 30 and 90. Furthermore, they include α-amylase, lipase, and C-reactive protein levels at 1 and 3 days, and both C-peptide and glycated haemoglobin levels at postoperative days 30 and 90. Moreover, pancreatic complications (i.e. graft pancreatitis, anastomotic leak and vascular complications including thrombosis, stenosis, and bleeding) will be compared, while fasting glucose after 90 days will be documented.

#### Liver

The secondary end points after liver transplantation include the absolute peak serum lactate dehydrogenase (LDH) level within the first 7 days after transplantation, the peak serum ALT and LDH levels, and serum bilirubin, aspartate aminotransferase (AST), ALT, LDH, and total albumin levels, and prothrombin time at postoperative day 90. Further biliary complications (i.e. the number of episodes of cholestasis, therapy for cholangitis, episodes of biliary leakage and intrahepatic and/or extrahepatic biliary strictures) will be assessed.

## Methods/design

This multicentre study is designed as a prospective, randomized and single-blinded trial. It is a phase III comparison study of organ preservation intended to demonstrate the noninferiority of Custodiol-N compared with Custodiol® in organ transplantation for the kidney, liver and pancreas. Study centres are the General, Visceral and Transplant Surgery, Department of Surgery, Medical University of Graz, Austria, and the Visceral, Transplant and Thoracic Surgery, Department of Surgery, Medical University of Innsbruck, Austria (Additional file 1).

### Inclusion criteria

#### Donor (liver, kidney, and combined kidney–pancreas) criteria

Deceased adult donors (≥18 years) fulfilling the criteria for organ donation are included in the study.

#### Patient (recipient) criteria

Patients (≥18 years) eligible for whole organ transplantation are included in the study.

### Exclusion criteria

Generally, patients with previous liver, kidney and combined kidney–pancreas transplantation are excluded.

#### Donor (liver, kidney, and combined kidney–pancreas) criteria

Donors whose organs are allocated to be used outside of Austria, a general refusal of organ donation, and being a donor after death due to cardiac causes are excluded.

#### Patient (recipient) criteria

Pregnant or lactating patients, recipients participating in any other interventional study (e.g. studies involving compounds/interventions aimed at the reduction of preservation and/or ischemia/reperfusion injury) and all combined allocations other than the pancreas and kidney are excluded from the study.

#### Kidney recipients

Double-kidney transplant patients, those on machine perfusion, and all patients with panel reactive antibody >0% according to the Kidney Disease Improving Global Outcomes 2009 guidelines are excluded.

#### Liver recipients

Machine-perfused organs are excluded from the study as well as recipients undergoing re-transplantation.

### Sample size

The study will continue until 412 kidney recipients and 202 liver recipients have been enrolled, treated and followed up. The number of combined kidney–pancreas transplants will be purely incidental and is estimated to be around 30. The overall duration for the trial is expected to be approximately 48 months. The duration of the trial for each participant is expected to be 3 months (for transplantation and a follow-up period of 90 days).

### Withdrawal of patients

Patients who discontinue participation in the clinical study on their own will be defined as premature withdrawals. Every patient has the right to withdraw their consent to participation in the clinical trial at any time and without giving reasons. This will not cause them to be disadvantaged. Nevertheless, the investigator must make every effort to find out the reasons why the patient has withdrawn from the study, while taking care not to compromise the patient’s rights. The time of withdrawal, the results available up to that time and, if known, the reason for the patient’s withdrawal are to be documented in the trial report form.

All ongoing adverse events (AEs)/serious adverse events (SAEs) in withdrawn participants have to be followed up until no more signs and symptoms are verifiable or the participant is in a stable condition. Patients who withdraw will not be replaced.

### Study medication

#### Treatment assignment

The reported organ donors are allocated according to the Eurotransplant guidelines without influence from the study. Only organs allocated to a patient who has signed the informed consent will be randomized.

Multiorgan donation is performed according to institutional guidelines. Organ perfusion is performed using Custodiol® as the standard preservation solution. Subsequently, organs allocated to a study centre with patients who have signed the informed consent will be randomized to either study medication. In case of simultaneous transplantation of the kidney and pancreas, both organs will be randomized together for the same study arm.

After randomization, back table perfusion with study medications will be performed via the renal artery for the kidney, the hepatic artery as well as the portal vein for the liver, and the mesenteric artery and portal vein for the pancreas using approximately 250–1000 ml of study medication per organ (Custodiol® or Custodiol-N). Subsequently, the grafts will be stored in 1000 ml of the study medication. The allocated study medication is provided to the recipient site. Before transplantation, back table perfusion using approximately 250–1000 ml of the study medication will be optionally performed.

